**At T0 (baseline)**
Intention for screeningPreferences for screening testCapacity to participate in screening (no serious health conditions preventing participants from undergoing screening)Previous screening recommendations of general practitionerKnowledge about screening for colorectal cancer (CRC)Demographics
**At T1 (intervention)**
Perceived susceptibility to CRCPerceived benefits of, and barriers to, screeningPerceived self-efficacy for screening testsParticipants’ opinions regarding the quality of the brochureAcceptance of the provided screening recommendations
**At T2 (follow-up at 6 months)**
Participants’ barriers to screening (only those who were not screened)

### Theoretical Framework for Understanding the Choice of Screening Test

Several of our outcomes are based on the health belief model [25], which posits that people are more likely to adopt a health-related behavior if they believe that they are vulnerable to the illness (perceived susceptibility) and that the illness is dangerous (perceived severity). Indeed, according to a recent meta-analysis [26], risk appraisals had a small to moderate effect on both the intention to adopt a health-related behavior and the behavior itself. However, the effect sizes for intention and behavior were nearly doubled in size when the interventions aimed at increasing participants’ self-efficacy and perceived efficacy of the recommended behavior [26].

We believe that participants’ screening behavior will largely depend on their perceived susceptibility to CRC as well as their beliefs about their self-efficacy and the efficacy of screening. These elements have been included in our intervention materials.

### CRC Risk Calculation and Risk Levels

The personalized 15-year CRC risk score will be calculated using the QCancer calculator [27]. The QCancer calculator is an open-source algorithm that was developed in the United Kingdom and validated on 2 large cohorts of 3.6 million and 2.1 million patients [28,29]. The QCancer algorithm is based on variables that were available from the patients’ primary care electronic health records. This covers many risk factors for CRC such as age, sex, and personal and family histories of cancers. However, diet and physical activity, which are 2 potentially important CRC risk factors, were not included in the algorithm because the information about them was not routinely collected and included in electronic health records [14]. The QCancer score was chosen because it was developed on a European population, it predicts CRC instead of advanced neoplasia, and it performed well in a large prospective validation study [13]. Despite some limitations, a systematic review showed that the QCancer score allows assigning an individual to the correct risk group with a probability of approximately 70% [14,15]. Although its predictive performance is not perfect, the QCancer risk score gives a good estimation of an individual’s risk level and allows the delivering of personalized recommendations for screening.

For this study, we modified the original algorithm slightly. Our adapted version includes the following factors to calculate the participants’ risk score: age; sex; tobacco and alcohol consumption; family history of CRC; personal history of breast cancer, uterine cancer, cervical cancer, or ovarian cancer for women and personal history of lung cancer, oral cancer, or blood cancer for men; having type 2 diabetes; and BMI values.

Ethnicity, postal code, ulcerative colitis, and colonic polyps will not be used in our adapted algorithm. Ethnicity and postal code have not been validated by studies for use in Switzerland and likely have different effects on CRC risk here than in the United Kingdom. For this reason, the option “White or not stated” will be used by default for all participants, and the field for postal code will be left blank. As our exclusion criteria include advanced adenoma and inflammatory bowel disease, we will indicate that our participants had neither ulcerative colitis nor colonic polyps. We have conducted tests to ensure the robustness of the QCancer score without these elements.

The obtained participant risk scores will be divided into 3 risk levels: low risk (<3%), moderate risk (3% to <6%), and high risk (≥6%).

These cutoffs are related to screening recommendations made to the participants and were based on the evaluation of risk and benefits related to the screening options.

### Intervention and Usual Care Materials

The intervention consists in communicating to the participants their 15-year CRC risk score and recommending the screening test most appropriate for their risk level using specially designed brochures (refer to Multimedia Appendix 4 for the English version of the brochure and Multimedia Appendix 5 for the French version). The intervention brochure is available in the following 3 categories: low CRC risk (<3%), with a recommendation to undertake the FIT; moderate CRC risk (3% to <6%), with a recommendation to either undertake the FIT or colonoscopy; and high CRC risk (≥6%), with a recommendation to undertake colonoscopy.

The intervention brochure provides the 15-year CRC risk score in comparison with that of an *average person* who has a similar profile; for example, an individual who has a CRC risk of 2% (low risk) receives the following message: “According to our estimations, 2 out of 100 people with the same profile as yours will get colon cancer in the next 15 years.”

This message is accompanied by a graphic representation of the risk score and the risk level. Refer to Multimedia Appendix 4 (English version) and Multimedia Appendix 5 (French version) for more information.

Clear screening recommendations presented in the intervention brochure aim to increase participants’ perceived self-efficacy for screening tests. We thus expect that participants at high risk will perceive that they are more susceptible to CRC and, therefore, will be more likely to undertake colonoscopy, which is the most accurate CRC screening test. By contrast, the participants at low risk are expected to perceive their susceptibility to CRC as lower and opt for the noninvasive FIT. To prevent the participants at low risk from declining screening, the brochure informs that zero risk does not exist and strongly recommends undertaking the FIT. No strong recommendations will be made to participants at moderate risk; therefore, the FIT and colonoscopy will be presented in the brochure as equal screening options.

To increase the participants’ perceived response efficacy, our intervention materials emphasize information about the advantages of the recommended test for their risk level. However, the intervention brochure does present an alternative to screening, thus offering a choice to the participants. Moreover, all intervention group participants will receive an information sheet suggesting that they discuss their risk level with their general practitioner.

The intervention brochure will contain recommendations corresponding to the risk level of each participant only. We expect that this will facilitate the understanding of the provided information, minimize reading effort, and enhance adherence to our recommendations. Refer to Table 2 for more information about the content of each brochure category. For the sake of brevity, the intervention brochures will not communicate the side effects or sensitivity of the tests. Both the FIT and colonoscopy are screening tests commonly used in Switzerland and are considered safe and efficient to significantly reduce CRC mortality if undergone within the recommended period (the FIT every 2 years and colonoscopy every 10 years).

The control brochure represents the usual brochure that the Vaud screening program provides to individuals eligible for CRC screening. This brochure recommends screening to all individuals beginning at age 50 years and presents both the FIT and colonoscopy as equal options. This brochure does not include either a personalized risk score or specific screening recommendations. This suggests that, in the control group, the screening tests will be chosen according to the participants’ preferences or after discussion with their primary care physician rather than in accordance with their risk level.

**Table 2 table2:** The different kinds of information presented in the printed materials.

Information presented in the brochure	Intervention brochure				Control brochure
	High risk	Low risk	Moderate risk		
Information about CRC^a^	Yes	Yes	Yes	Yes	
Information about screening benefits	Yes	Yes	Yes	Yes	
Explanation concerning risk levels and how they can be calculated	Yes	Yes	Yes	No	
Personalized risk score	Yes	Yes	Yes	No	
Screening recommendations	Personalized: colonoscopy recommended; the FIT^b^ as an alternative	Personalized: the FIT is recommended; colonoscopy as an alternative	Personalized: the FIT and colonoscopy are equal options	General: the FIT and colonoscopy are equal options	
Explanations why recommended tests are appropriate	Yes	Yes	Yes	No	
Short instructions about how to undertake the FIT and how to prepare bowel for colonoscopy	Yes, instructions for colonoscopy only	Yes, instructions for the FIT only	Yes, instructions for both tests	Yes, instructions for both tests	
Warning that risk increases with age and encouraging statements to maintain a healthy lifestyle	Yes	Yes	Yes	No	
Suggestion to consult a physician if cancer symptoms occur	Yes	Yes	Yes	Yes	
Information about health insurance coverage of the screening tests	Yes	Yes	Yes	Yes	

^a^CRC: colorectal cancer.

^b^FIT: fecal immunochemical test.

### Qualitative Interviews

Semistructured qualitative interviews will be conducted by telephone with a purposive sample of approximately 20 participants using a previously elaborated interview guide until we achieve thematic saturation. The interviews are based on the user-experience “honeycomb” framework described by Morville [30], and they aim to obtain detailed information about the quality of the brochure and the acceptability of the provided screening recommendations. We will be especially interested in the following information: (1) whether the brochure is useful for decision-making about the screening tests; (2) whether participants feel that the brochure improved their knowledge about CRC and screening; (3) whether the information is clear, easy to understand, and credible; and (4) whether the brochure satisfies the participants or whether they have suggestions to improve it.

Purposive sampling will be based on study arm, sex, age, risk level, knowledge of the French language, and reported preferences for the screening test.

### Randomization and Blinding

Randomization will be carried out automatically via the REDCap randomization module programmed by the trial statistician. We will apply a stratified block randomization strategy with a block factor of 8 to prevent a possible imbalance between the control and intervention groups, especially among participants at high risk. The participants will be blinded to the group allocation. They will be told that the study compares 2 slightly different brochures about CRC screening options; however, the nature of the intervention will not be disclosed. The investigators will not be blinded, but, owing to the automatic randomization, they will not be able to influence the participants’ group allocation. The analysis of the main study outcome will be performed by the trial statistician who will be blinded to the participants’ allocation.

### Ethics Approval

The study protocol (project ID 2021-02431) was approved by the ethics committee of the canton of Vaud on March 2, 2022. All the important protocol modifications will be documented and communicated to the ethics committee along with the intermediate and final reports.

### Steering Committee and Trial Monitoring

The trial is supervised by a steering committee composed of a gastroenterologist, a general practitioner, an epidemiologist, and psychologists, as well as experts in shared decision-making and statistical modeling. The members of the steering committee are in charge of approving the trial’s methodology and data analysis plan, and they also contribute in the preparation of oral and written communication materials.

The trial is monitored by an institutional team for trial monitoring that is independent from the trial sponsor and competing interests. The monitoring team will check the quality of collected data as well as conformity with the study protocol. At least 3 site visits are planned, following recommendations from the Swiss Clinical Trial Organization for low-risk trials.

### Statistical Analyses

#### Sample Size Estimation

We expect that 60% of the eligible individuals will be at low risk for CRC, 30% at moderate risk, and 10% at high risk, based on approximate calculations carried out with the UK biobank cohort. The actual distribution of CRC risk factors, and hence 15-year risk scores, in the Vaud population eligible for the screening program is not known.

We also expect that in the intervention group, individuals will be more likely to undertake the appropriate screening test, whereas in the control group, the choice of screening test will not differ among the risk levels (Table 3).

Thus, to detect a difference of 10% (ie, between 46% and 56%) at α=5%, a sample size of 392 individuals in each arm is required to reach 80% power. Assuming approximately 10% attrition, we plan to recruit 440 individuals in each arm (a total of 880 individuals). Our estimation of 10% attrition is based on the results of previous longitudinal studies conducted in the canton of Vaud.

We will invite individuals who have not previously been invited to the Vaud CRC screening program. At the time of sending out the invitation, we will not know whether they are eligible for screening, principally because they may already be up to date with screening or may have had a high-risk polyp needing colonoscopy surveillance. Thus, we plan to send out approximately 4300 invitations; we expect 1400 (32.56%) to respond. Of these 1400 participants, we anticipate that 880 (62.86%) will be eligible for the study (Figure 1). In case of a low response rate, we will send out an additional 2000 invitations.

**Table 3 table3:** Hypothesized size of each group as a proportion of the eligible population and predicted changes in screening choices with personalized recommendations. Group sizes have been chosen to provide sufficient statistical power.

Arm and risk level			Eligible population, %		Choose colonoscopy, %		Choose FIT^a^, %		None, %		Colonoscopy, n/N		FIT, n/N		None, n/N		Overall uptake, %		Appropriately screened, % (n/N)		Overall proportions by randomization
**Control** **(n=392)**																					
	Low	60		34.9		34.9		30.2		82/235		82/235		71/235		70		35 (82/235)		Appropriate screening: 46% (179/392)	
	Moderate	30		34.7		35.6		29.7		41/118		42/118		35/118		70		71 (83/118)		Overall uptake: 70%	
	High	10		35		35		30		14/39		14/39		11/39		70		35 (14/39)		—^b^	
**Intervention** **(n=392)**																					
	Low	60		20.4		49.8		30.2		48/235		117/235		71/235		70		50 (118/235)		Appropriate screening: 56% (220/392)	
	Moderate	30		34.7		35.6		29.7		41/118		42/118		35/118		70		70 (82/118)		Overall uptake: 70%	
	High	10		50		25		25		20/39		10/39		9/39		75		50 (20/39)		—	

^a^FIT: fecal immunochemical test.

^b^Not available.

#### Data Collection

Trial personnel will be trained in good clinical practices and data management. The research team will be provided with the precise guidelines for the inclusion and exclusion criteria, data collection and analysis, and the handling of missing data.

For data collection, we will use 2 validated questionnaires or questionnaires pretested in previous studies. All study materials, including questionnaires, have been reviewed and approved by our citizen advisory group.

All answers to the questionnaire in paper format will be manually entered into the REDCap platform, and 20% of the entries will be checked by another member of the research team. Qualitative interviews will be conducted by a trained team member, recorded, and transcribed. For quality assurance, dual independent coding will be used for 20% of the transcripts, purposively selected. Data triangulation will be used as relevant. Investigator triangulation will also be conducted.

Quantitative and qualitative data will be coded using unique participant identifiers previously generated via the IDGenerator [21]. Paper questionnaires and consent forms will be stored in the investigator site file. Coded data and participant identification lists will be stored separately. Participants’ data will be accessible to authorized personnel only.

Although our trial presents low risk for participants, we will collect information about adverse events; for instance, we will collect information about rectal bleeding or hospitalization after colonoscopy and participants’ anxiety related to the intervention and control materials, as well as the adverse events registered by the Vaud screening program. Serious adverse events will be documented and reported within 24 hours to the sponsor-investigator of the study. Serious adverse events that could be attributable to the trial intervention will be reported to the ethics committee within 15 days.

#### Quantitative Data Analysis Plan

The study data will be summarized across all participants by group and by risk level. Continuous and count variables will be summarized as mean (SD) or median (IQR) and categorical variables as number (percentage). To test randomization quality, differences on the baseline variables will be examined using a 2-tailed *t* test for continuous variables and a 2-tailed chi-squared test for categorical variables.

Self-reported appropriate screening uptake will be analyzed using a 2-tailed chi-squared test and controlled for the CRC risk level. Data analysis will be performed using R statistical software (R Foundation for Statistical Computing) [31] and Stata 16 software (StataCorp LLC) [32].

For the primary outcome, participants lost to follow-up will be considered as having refused to participate in screening. If there seems to be differential loss to follow-up between the intervention and control groups, we may perform multiple imputation based on baseline factors as an exploratory analysis. For other secondary outcomes, data will be considered missing completely at random.

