**Assessments**					
	Baseline variables: eligibility, risk factors for CRC, previous screening recommendations from a GP^e^, knowledge about screening for CRC, demographics, and contact information	✓			
	Main outcome variables: FIT^f^ uptake, colonoscopy uptake or appointment for colonoscopy				✓
	Secondary outcome variables				
	Intention for screening	✓		✓	✓
	Results of the undertaken screening test				✓
	Self-efficacy for screening tests			✓	
	Emotional reaction to the received risk score			✓	
	Perceived barriers to screening			✓	✓
	Perceived benefits from screening			✓	
	Perceived susceptibility for CRC			✓	
	Quality of the brochure and acceptability of the screening recommendations			✓	

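### Baseline t and chi-squared tests are a poor check of randomisation quality when allocation is automatic, stratified and blocked

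*Protocol article*

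**What the plan says.** The Quantitative Data Analysis Plan gives the baseline comparisons an explicit inferential purpose: "To test randomization quality, differences on the baseline variables will be examined using a 2-tailed" *t* test or chi-squared test, according to the type of variable. The same section already plans descriptive summaries by arm and by risk level.

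Randomization and Blinding describes the allocation: "Randomization will be carried out automatically via the REDCap randomization module programmed by the trial statistician", using a "stratified block randomization strategy with a block factor of 8". The Abstract says that randomisation takes place within each of the three risk strata. Of the investigators, the article says that "owing to the automatic randomization, they will not be able to influence" the allocation.

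The candidate variables are spread over three places:
- Table 1: "Baseline variables: eligibility, risk factors for CRC, previous screening recommendations" and further items, including knowledge and demographics.
- CRC Risk Calculation and Risk Levels: the risk-score inputs, beginning "age; sex; tobacco and alcohol consumption; family history of CRC".
- The textbox of additional measures: the items collected at T0, among them screening intention, test preference and capacity to be screened.

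For the baseline tests themselves, the article states no significance threshold, list of variables, multiplicity rule or consequence of a significant result.

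**The concern.** A significance test asks whether a difference could plausibly be due to chance. Under the allocation described, if it is implemented as described, chance is the only possible source of a baseline difference. The null hypothesis is then true, and small p-values appear at their nominal rate whatever the merits of the randomisation. With a dozen or more variables, one or more such p-values is an ordinary result.

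The opposite reading is also unsafe. A p-value above 0.05 does not measure whether an imbalance matters for the outcome. Baseline intention and test preference plausibly predict which test a participant takes, and an imbalance in either could matter without reaching significance. For variables that feed the risk score, the strata already force some balance, so an unstratified test rejects less often than its nominal level suggests.

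At stake is what the report says about randomisation: doubt cast on a sound allocation, or reassurance that the tests cannot give.

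**Working it through.** **1. The article's own figure.** No figure is given for the baseline tests. The only stated alpha belongs to the sample size: "to detect a difference of 10% (ie, between 46% and 56%) at α=5%, a sample size of 392 individuals in each arm". With p1 = 0.46, p2 = 0.56, mean 0.51, two-sided 5% and 80% power:

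n = [1.960·√(2·0.51·0.49) + 0.842·√(0.46·0.54 + 0.56·0.44)]² / 0.10² ≈ 391.1, rounded up to 392 per arm.

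This reproduces the stated 392. Allowing for 10% attrition, 392/0.9 gives 436, close to the planned 440. The sample size is not affected by this point. A 5% threshold for the baseline tests is an assumption made here.

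**2. Number of variables.** Merging the three lists gives:
- Risk-score inputs (8): age, sex, tobacco, alcohol, family history, personal cancer history, type 2 diabetes, BMI.
- Other T0 items (5): general practitioner recommendation, knowledge, intention, test preference, capacity.
- Demographics: at least 1 further item.

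That makes about 14. The article does not say which of these will be tested, so a range is shown.

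**3. Chance of at least one p<0.05 under a sound randomisation.** With k independent tests at 5%, this is 1 − 0.95^k:

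| k | Chance of at least one |
|---|---|
| 8 | 34% |
| 10 | 40% |
| 14 | 51% |
| 20 | 64% |

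Independence is an approximation. A simulation (2,000 trials per setting, stratified blocks of 8, 15 variables, assumed prevalences, correlations and risk-score weights) gave 49% to 51% at N = 880. At N = 515, the enrolment reported in Results, it gave 50% to 51%. Each trial had on average about 0.7 false flags.

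**4. Variables that drive the strata.** Stratification removes between-stratum variation from the arm difference, while the standard error of an unstratified test still includes it. In the same simulation, age was the assumed main driver of the score, and its *t* test rejected in 0.2% to 0.3% of trials instead of 5%. The size of this effect depends on the assumed weights. The direction does not.

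**5. What the tests can detect.** For one two-sided 5% *t* test on a standardised difference d, with N/2 per arm, power ≈ Φ(d·√(N/4) − 1.96):

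| d | N = 880 | N = 515 |
|---|---|---|
| 0.1 | 32% | 21% |
| 0.2 | 84% | 62% |
| 0.3 | 99% | 93% |

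A large imbalance would probably be seen. An imbalance of 0.1 SD would usually pass.

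**The case against.** The strongest defence is that describing the intended allocation does not prove that it was carried out. The null holds only if the module was programmed and run correctly, and the tests ask exactly that. This stands in part. A reader might infer that the tests cannot tell a good allocation from a bad one, but the power figures contradict this: at 0.3 SD, one test has 93% to 99% power. The narrower statement is that reading any p<0.05 as a flag has specificity of only about 50% with some 14 variables, and that non-significance does not certify the allocation.

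Second, the flagging rule is not in the article, which says only that differences will be examined. This also stands. A reader might take a false alarm about half the time as a property of the plan. It follows only from an assumed threshold, an assumed rule and an assumed count.

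Third, a reader might infer that the tests will steer covariate choice or weaken the primary comparison. The text supports neither. It does not let the baseline tests select covariates, and the primary analysis accounts for risk level whatever they show. Nor does it say that the tests are run within strata, so a complaint about low power in the small high-risk stratum would rest on an analysis that is not stated.

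Finally, independent monitoring of data quality and protocol conformity is already planned (Steering Committee and Trial Monitoring). That supports checking the process and leaves the tests little to add.

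**Conclusion.** The point holds in a limited form and is minor. The stated method does not serve its stated purpose well: if the allocation ran as described, a small baseline p-value is a chance finding, and a large one does not show that an imbalance is unimportant. A sound randomisation would be flagged about 34% to 64% of the time, with about 51% for the items named. This assumes 8 to 20 approximately independent tests at 5% each, with any p<0.05 taken as a flag. Tests on strong risk-score inputs such as age run below their nominal level. A gross failure would probably still be detected. The sample size, the primary estimate and its test are untouched. Only the conclusion drawn about randomisation quality is affected.

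**What to change.** - Delete the baseline *t* and chi-squared tests, and their stated purpose, from the Quantitative Data Analysis Plan.
- Keep the descriptive baseline summaries by arm and risk level that are already planned, optionally adding standardised differences.
- Verify randomisation from the process: compare the REDCap allocation record with the stratified block-of-8 list, and check the arm counts per stratum.
- Base any covariate adjustment of the primary result on baseline variables already collected, for example intention or test preference. Fix the list before the outcome is analysed by arm and apply it whatever balance is observed.

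The cost is one sentence of plan wording and a check of an existing record. No new data are needed and there is less testing to report. Results states that data collection has been completed. If analysis has already begun, the baseline table can still be reported without these p-values being read as evidence on the allocation.
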